# Social group and health care provider interventions to increase the demand for malaria rapid diagnostic test among community members in Ebonyi state, Nigeria: study protocol for a cluster randomized controlled trial

**DOI:** 10.1186/s13063-019-3620-0

**Published:** 2019-10-10

**Keywords:** MRDT, Fever, Malaria, Demand, Social groups, Providers, Community members

## Abstract

**Background:**

The World Health Organization recommended (in 2010) universal testing for suspected malaria, due to some fundamental changes in malaria trends such as the declining incidence of malaria in high-burden countries, the emergence of parasite resistance to anti-malarial drugs especially artemisinin-based combination therapies (ACTs) and the increased availability of diagnostic testing such as the malaria rapid diagnostic test (MRDT). The Nigerian government has long adopted this recommendation and with the support of foreign partners has scaled up the availability of MRDT. However, the malaria/MRDT rate in the communities is still far short of the recommendation. This study aims to evaluate the effectiveness of social group and social group/provider interventions in increasing the demand (use and/or request) for MRDT among community members with fever or malaria-like illness in Ebonyi state, Nigeria.

**Methods:**

A three-arm, parallel, stratified cluster randomized design will be used to evaluate the effect of two interventions compared to control: control involves the usual practice of provision of MRDT services by public primary healthcare providers and patent medicine vendors; social group intervention involves the sensitization/education of social groups about MRDT; social group/provider intervention involves social group treatment plus the training of healthcare providers in health communication about MRDT with clients. The primary outcome is the proportion of children under 5 years of age with fever/malaria-like illness, in the 2 weeks preceding a household survey, who received MRDT. The co-primary outcome is the proportion of children ages 5 years and above and adults (excluding pregnant women) with fever/malaria-like illness, in the 2 weeks preceding a household survey, who received MRDT. The primary outcome will be assessed through household surveys at baseline and at the end of the study.

**Discussion:**

The pragmatic and behavioural nature of the interventions delivered to groups of individuals and the need to minimize contamination informed the use of a cluster-randomized design in this study in investigating whether the social group and social group/provider interventions will increase the demand for MRDT among community members. “Pragmatic” means the interventions would occur in natural settings or real- life situations.

**Trial registration:**

ISRCTN, ISRCTN14046444. Registered on 14 August 2018.

**Electronic supplementary material:**

The online version of this article (10.1186/s13063-019-3620-0) contains supplementary material, which is available to authorized users.

## Background

The World Health Organization (WHO) recommended in 2010 that all patients suspected of having malaria receive prompt parasitological testing (with microscopy or malaria rapid diagnostic test (MRDT)) to confirm diagnosis before treatment [1]. Treatment based on presumptive diagnosis should only be considered when parasitological diagnosis is not accessible [1]. However, patients suspected of having severe malaria, including children and high-risk groups, should receive immediate treatment on presumptive grounds when the parasitological diagnostic test result is delayed by up to 2 hours or more [1]. The WHO recommendation for universal testing is based on some fundamental changes in malaria trends worldwide such as the declining incidence of malaria in high-burden countries, the emergence of parasite resistance to anti-malarial drugs especially to artemisinin-based combination therapies (ACTs) and the increased availability of diagnostic testing such as MRDT [2, 3]. Though malarial parasite resistance to ACTs has been detected in the Greater Mekong Area [4–7], ACTs are still effective because the parasite resistance is either in the form of delayed parasite clearance or resistance to the partner drug [4, 6, 7]. However, widespread over-treatment of malaria with ACTs as a result of inaccurate presumptive diagnosis is likely to compound the problem.

The use of MRDT is a key part of the strategy for universal parasitological diagnostic testing recommended by the WHO [1, 2, 8, 9] and this has been demonstrated in some countries like Senegal [10, 11] and Lao People’s Democratic Republic [10]. Many countries have started emphasizing parasitological diagnostic testing as the basis for malaria treatment and have been scaling up the availability and use of MRDT, especially in the public sector. It is worth noting that uptake and use of MRDT can only remedy over-treatment with ACTs when providers (and patients) respond appropriately to negative test results [12]. Accurate diagnosis of malaria is important in all settings [1, 13]: in settings where malaria is endemic, highly sensitive diagnosis is essential, especially in children in whom falciparum malaria can quickly become fatal; in all settings, highly specific diagnosis will minimize unnecessary anti-malarial treatment and improve the diagnosis of other causes of fever. The WHO recommended a policy of “test, treat and track” in 2012 to improve the quality of care and surveillance [3].

Malaria is a disease of public health importance in Nigeria. It is endemic, with varying endemicity and risk across the regions of the country [14–16]. Nigeria also bears about 29% of the malaria burden in Africa [15] and more than 25% of global malaria cases and of global mortality from malaria in 2015 [4]. Malaria rapid diagnostic test (MRDT) was introduced in Nigeria during the period of the national malaria strategic plan 2009–2013, with the aim of extending MRDT to all public and private sector health facilities including at the community level [14, 17, 18]. Aligning with the WHO’s Global Technical Strategy (GTS) for Malaria 2016–2030, the current national malaria strategic plan 2014–2020 aims for Nigeria to achieve a pre-elimination status and reduce malaria mortality to zero by 2020 [14]. One of the objectives of the 2014–2020 national malaria strategic plan is to, by 2020, perform MRDT or microscopy for all patients with suspected malaria who seek medical care, and the strategic actions include to ensure the availability of and access to MRDT (and or microscopy) at public and private health facilities; to build the capacity of healthcare personnel and to create demand for the utilization of parasitological diagnostic testing via actions targeted at both the health workers and the general public [14].

The WHO’s recommendation of universal parasitological testing has long been adopted by countries around the world, including Nigeria. The Nigerian government (with the support of foreign partners) has scaled up the availability of MRDT in recent years but significant challenges remain. The malaria/MRDT rate in the communities is still unacceptably low. In the recent Nigeria Malaria Indicator Survey (NMIS) 2015 [15], the percentage of febrile children under 5 years of age who (in the preceding 2 weeks) were reported to have had blood taken from a finger or heel for testing (indicating a malaria test) was 13% nationally and 11% in the south-east, indicating a very low test rate in the south-east zone, which includes Ebonyi state. Also, the World Malaria Report 2016 [19] reported that among 22 nationally representative surveys in sub-Saharan Africa between 2013 and 2015, the median percentage of febrile children who received a finger or a heel stick, indicating that a malaria diagnostic test was performed, was 51% in the public sector, 40% in the formal private sector and 9% in the informal private sector (which includes the patent medicine vendors (PMVs)).

Also, the scale-up has mainly been in the public health sector (and only to a lesser extent in the private sector) despite the fact that in Nigeria the majority of febrile patients (adults and children), especially from the less educated, lower socio-economic groups and in the rural settings, first seek care in the informal private sector (from the PMVs) [15, 20–22] where they are more likely to receive inappropriate treatment for malaria [15, 20–24], usually based on presumptive diagnosis [22–24]. This problem is similar across sub-Saharan African countries [4, 19, 25–27].

Moreover, following the recommendations in 2006 [28] for the use of ACTs as the first-line anti-malarial drug, there has been a progressive and widespread increase in the use of ACTs across Nigeria [15, 20, 29] and sub-Saharan African countries [4, 19] that is associated with over-treatment (over-prescription). This has heightened the risk of selection pressure and drug resistance. Though there is an increased rate of testing in the public facilities (which is still below recommendation), the test rate in the private sector, especially the informal private sector such as the PMVs, is at best negligible and the problem of non-adherence to negative test results is limiting the remedy to over-prescription of ACTs by MRDT [12].

The demands of patients and caregivers significantly influence the treatment decisions of the providers in general [30–33] and following (negative) MRDT results in particular [30, 33] (as providers appear to be influenced by their perception of patients’ expectations/wants in cash and kind). Also, the scaling up of MRDT for universal parasitological testing requires behavioural change interventions targeted at healthcare providers [9, 33], patients, families and community members [9]. However, there is a paucity of literature on interventional studies to increase patients’ and caregivers’ demands for MRDT the world over. Most studies have focused on the diagnostic accuracy of MRDT, uptake and use of MRDT among providers, appropriate response to negative test results, improvement in malaria treatment according to treatment guidelines and the cost-effectiveness of MRDT compared to presumptive and/or microscopic diagnosis, etc. This study aims to educate/sensitize social groups about MRDT and to train healthcare providers in health communication about MRDT with patients/caregivers, to determine whether these can increase the demand (use and/or request) for MRDT among community members in Ebonyi state, Nigeria, who have fever or malaria-like illness. The findings will inform health policy decisions in Ebonyi state and in Nigeria as a whole in her strive to achieve universal access to parasitological diagnosis of malaria together with the global communities.

## Methods/design

The study is a pragmatic, single-centre, three-arm, parallel, open-label, stratified cluster-randomized controlled trial with 1:1:1 allocation. “Pragmatic” means the study (interventions) would occur in natural settings or real-life situations. A cluster is defined as a geographical community or village(s)/settlement(s) (with at least 250 households or a population of 1500 people) serving as the proximate catchment area for at least one public primary health facility and one PMV within the study sites/strata in Ebonyi state.

A three-arm parallel design, with an equal number of clusters in each arm and an equal sample size in each cluster, will be used to assess the effect of two interventions compared to control:
Control arm**:** no intervention. This arm involves the usual practice of provision of MRDT services by individual healthcare providers (in public health facilities and PMVs) with basic training in MRDT. The PMVs that have offered the MRDT service previously but are not currently doing so will be re-supplied with MRDT kits to resume provision of MRDT services for the study period.Social group arm: social group intervention. This arm involves control treatment plus the sensitization and education of social groups about MRDT.Social group/provider arm: social group/provider intervention. This arm involves control treatment and the sensitization and education of social groups about MRDT plus the training of healthcare providers in health communication about MRDT with patients/caregivers (clients).

The trial protocol development was guided by the Standard Protocol Items: Recommendations for Interventional Trials (SPIRIT) 2013 checklist (see Additional file 1).

### Study area

The study is being conducted in three sites/strata in Ebonyi state, south-eastern Nigeria. Ebonyi state is located in the south-east geopolitical zone of Nigeria between latitude 5^0^ 40′ and 6^0^ 54′ N and longitude 7^0^ 30′ and 8^0^ 30′ E, with a land area of 5953 km^2^ [34]. It shares borders with Benue state to the north, Enugu state to the west, Cross River state to the east and Imo and Abia states to the south [34, 35]. The State lies in the plains of Cross River, with the rainy/wet season from April to October and dry/*harmattan* season from October to March [34]. Floods often occur during the rainy season due to poor drainage systems, stagnant rivers and ponds, which expose the State to mosquito infestations and a high malaria burden [34]. The prevalence of malaria in the State among children under 5 years of age as reported in the 2015 NMIS was 51% (diagnosed using MRDT) and 30% (diagnosed using microscopy) [15]. A total of 305,879 laboratory-confirmed cases of malaria were reported between December 2013 and November 2014 in the State’s malaria surveillance system, which only covers the public health sector [36]. The vegetation of the State is mostly savannah in the drier northern part and forests in the wetter southern part [34].

The State’s projected population for 2016 was 2,897,401 (based on the 2006 national census figure and a growth rate of 2.8%) with male inhabitants making up 48.62%, female inhabitants 51.38% and children under 5 years of age 20% [34]. The people of Ebonyi are primarily of the Igbo language and ethnic extraction with ten dialects/minor languages spoken across the State [35]. English, especially its local variant, the pidgin, is a widely spoken language in the State. People of other languages and ethnic groups in Nigeria also live in the State, especially in the capital and urban areas. Most inhabitants practice Christianity [35]. The State is divided into three senatorial zones (Ebonyi north, Ebonyi central and Ebonyi south), with 13 Local Government Areas (LGAs) (with Abakaliki LGA as the administrative and political capital), 64 development centres, 138 autonomous communities and 215 political wards [34]. Each autonomous community has a traditional ruler and consists of autonomous villages each having a village head called the chairman. Each autonomous village is made up of smaller villages or settlements each having a village/settlement head.

The public sector is the main driver of the State economy and agriculture is the major occupation [35]. The State has several solid mineral resources (including lead), crude oil and natural gas [35] but there are few large-scale commercial mines and industries [34, 35]. The State is called “the salt of the nation” because of huge salt deposit at the Okposi and Uburu Salt Lakes [35]. Traditional industries and works of art include blacksmithing, pottery works and wood works (carved doors, stools, walking sticks, traditional flutes, wooden mortars and pestles) [35].

Health care in Ebonyi state (like other states in Nigeria) is provided by the public and private sectors under the overall guidance of the federal government through the Federal Ministry of Health (FMoH) (and its agencies) and the national council on health. The federal government (through the FMoH) provides health services in the State through tertiary health facilities. The State government (through the State Ministry of Health (SMoH)) provides health care through secondary health facilities (general hospitals). The State government also supports the local governments in providing primary health care (PHC) through PHC facilities. The Ebonyi State Malaria Elimination Program (SMEP), within the department of public health in the SMoH, coordinates the efforts to combat malaria in the State.

Other healthcare service providers recognized by the National Health Act 2014 include the private healthcare providers, traditional healthcare providers and alternative healthcare providers [37]. These can be grouped as the private health sector and subdivided as formal private sector (private hospitals and clinics) and informal private sector (pharmacies, PMVs, traditional healers and alternative healthcare providers) [4]. The majority of febrile patients, especially from the lower socio-economic groups, seek care primarily in the informal private sector [14, 16, 18].

The three study sites/strata consist of the three senatorial zones: Ebonyi north, Ebonyi central and Ebonyi south. Ebonyi north consists of four LGAs with a 2016 population of 998,473 [38]. Two of these LGAs, Abakaliki LGA (the state capital) and Ebonyi LGA, have contiguous urban areas that jointly constitute the city/metropolis of Ebonyi state. However, Ebonyi north is a predominantly rural area. The vegetation is mostly savannah and it is drier than the other sites. Ebonyi central consists of four LGAs with a 2016 population of 861,554 [38] and is a predominantly rural area. The vegetation changes from savannah towards forests and the weather become wetter as one moves through this central zone southward towards the southern zone. Ebonyi south consists of five LGAs with a 2016 population of 1,037,376 [38] and is also predominantly rural. Malaria is endemic in the three sites, with year-round transmission and a high burden of malaria.

### Participants and participant timeline

#### Participants

##### Clusters

Clusters eligible to participate in the study include villages/settlements (a community) that have at least one eligible public primary healthcare facility and one eligible PMV (see below) and are easily accessible (close to a motorable road) even in the rainy season. Clusters either participating in or that have participated in any similar interventions within the preceding year will be excluded from participating in the study. Clusters that are too close (less than 15 km apart) and are not separated by a buffer area or natural barrier, and urban clusters (in cities/towns) will be excluded from participating in the study to minimize contamination between clusters within strata [39, 40]. Non-consenting clusters will also be excluded from participating in the study.

##### Social groups

Social groups are any set of persons within society with particular demographic, economic or social characteristics [41]. Examples of social groups include women associations/meetings, village meetings, men associations, youth associations, market/trade unions, elders’ fora, parent-teacher associations, etc. Social groups that are recognized by cluster heads/authorities will be included to participate in the study and non-consenting social groups will be excluded.

##### Primary health facilities and individual healthcare providers

Eligible public primary health facilities are those providing MRDT services, maternal and child healthcare services including immunization, attending to at least an average of four patients with fever (or suspected malaria) per day and having at least two staff that are at least junior community health extension workers (JCHEWs). Individual public healthcare providers involved in the diagnosis (and treatment) of malaria in these facilities are eligible. Eligible PMVs are those with basic training in MRDT services and either currently offering or having previously offered MRDT services. Non-consenting health facilities and individual providers will be excluded from the study.

##### Households and community members

Households will be eligible to participate in a population-based household survey if there is a report of any case of fever or suspected malaria among children under 5 years of age, children age 5 years and above and adults (excluding pregnant women) in the household in the 2 weeks preceding the survey. Consent will be obtained in each household, from the mother of the house or the female primary care-giver, who will be the respondent in the survey. Non-consenting households will be excluded from the survey. After the baseline household survey, community members that have resided in the community for at least 2 years will be eligible to participate in a focus group discussion (FGD). Non-consenting community members will be excluded from the FGD.

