### The sensitization and education of social groups

The social group intervention will involve the sensitization and education of social groups within each cluster in the social group arm. There will be three episodes of group discussion/interaction, one per month, with each social group during the intervention period of 3 months. Health education messages designed to change incorrect beliefs and perceptions, promote correct beliefs and perceptions, increase knowledge and promote key actions will be communicated to social group members in an interactive session/group discussion. The health education message is adopted from a national framework [42] and modified for the study.

Each discussion will be a 1-hour event. One investigator will moderate each discussion with a group discussion guide. In order to make the intervention more pragmatic and to optimize adherence to the trial intervention, the discussions will take place at the usual meeting time of each social group, or at an agreed time, and at their usual meeting point/venue or at a central location as is most convenient for the participants. The intervention will be discontinued for a social group or cluster whenever such a request is made by the respective social group head/leader or cluster head/authority. The first episode will be divided into 7 sub-headings, viz. (1) introduction, (2) individual beliefs and opinions, (3) key facts about malaria, (4) key facts about MRDT, (5) demonstration of testing with MRDT kit, (6) key actions to practice and promote and (7) closing remarks. The moderator will explain the research problem and objectives to the participants and the broad role the participants (social group members) are expected to play in addressing the problem. Each participant will then share his/her beliefs and opinion about malaria with respect to the cause, symptoms, complications/fatalities, diagnosis, treatment, where to seek care and why and prevention. The discussion will explore the reasons for and against these views and there will be questions and answers from participants. The moderator will then highlight the key facts about malaria. Key facts about the MRDT will also be highlighted and discussed. Malaria rapid diagnostic test (MRDT) will be demonstrated in volunteer participants, the procedure will be explained, the results interpreted and explained to them and those that test positive will be treated with an ACT.

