The moderator will then highlight and discuss the key actions that the participants should exercise and promote as individuals, social group members, opinion leaders, parents, heads of households, family members, friends and relatives, neighbours, etc. These actions include recognizing the symptoms of malaria especially in children under 5 years of age, promptly seeking care with providers that carry out MRDT (preferably in the public primary health facilities) and requesting the “simple test” for malaria (MRDT), receiving the test, asking for the result, and receiving treatment for malaria (with ACTs) only when the test is positive, making sure children under 5 years of age receive treatment within 24 hours of on-set of fever and acquiring and giving the appropriate ACTs at the correct dose for the correct number of days. The moderator will then make closing remarks and thank the participants for their time.

The second and third episodes will take a similar format as the first but will focus more on re-emphasizing the key facts and actions to practice and promote so as to reinforce participants’ knowledge and attitudes. The participants will be encouraged to share their experiences in the preceding 4 weeks for discussion and clarification. Visits to the social groups will end with the third episode of group discussion. However, group members will be able to contact the investigators on their cell phones if they still require clarification on malaria and MRDT during the subsequent months.

Other supportive interventions will include reminder text messages sent at least weekly to social group members that have cell phones, regular phone calls to social group heads (to urge them to remind and encourage the group members during meeting sessions) and regular visits by a provider (PMV or public) to the scheduled meetings of each social group for provision of MRDT services and ACTs for positive results.

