### Objectives

The primary objectives include:
To evaluate the effectiveness of the sensitization/education of social groups about MRDT (social group intervention) in increasing the demand (use and/or request) for MRDT compared to usual practice (control)To evaluate the effectiveness of the sensitization/education of social groups about MRDT and training of providers in health communication about MRDT with patients/caregivers (social group/provider intervention) in increasing the demand for MRDT compared to usual practice (control)To evaluate the effectiveness of the social group/provider intervention in increasing the demand for MRDT compared to the social group intervention

The secondary objectives include:
To evaluate the effect of the interventions on the care-seeking practices and pattern of anti-malarial drug use among community membersTo assess the effect of the interventions on the knowledge and opinions of respondent female heads of households (female primary care givers) about malaria and malaria diagnosisTo evaluate the effect of the interventions on the number of patients with suspected malaria visiting the public primary health facilitiesTo assess the effect of the interventions on the knowledge and opinions of healthcare providers and their practice of health communication about malaria and malaria diagnosisTo evaluate the cost-effectiveness of the interventionsTo assess the level of demand (use and/or request) for MRDT, care-seeking practices and pattern of anti-malarial drug use among community members with fever or malaria-like illnessTo assess the level of knowledge and opinions of female heads of households (female primary care givers) and of healthcare providers about malaria and malaria diagnosisTo ascertain the factors that influence the demand for MRDT among community members

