### Outcome measures

#### Primary outcome

The primary outcome is the proportion of children under 5 years of age with fever or malaria-like illness, in the 2 weeks preceding a population-based household survey, who received MRDTThe co-primary outcome is the proportion of children ages 5 years and above and adults (excluding pregnant women) with fever or malaria-like illness, in the 2 weeks preceding a population-based household survey, who received MRDT

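### Entry to both co-primary denominators rests in part on the respondent's opinion that an illness was malaria, which the intervention is meant to change, so the tested proportion can differ between arms without a change in testing

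*Protocol article*

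**What the plan says.** Under 'Households and community members', a household is eligible "if there is a report of any case of fever or suspected malaria among children under 5 years of age", or among older children and non-pregnant adults, in the 2 weeks before the survey. Consent is taken "from the mother of the house or the female primary care-giver, who will be the respondent in the survey".

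Under 'Primary outcome', the article names "the proportion of children under 5 years of age with fever or malaria-like illness, in the 2 weeks preceding a population-based household survey"; the numerator is those given the test. The co-primary outcome uses the same illness wording for older children and adults. Suspected malaria at entry has thus become malaria-like illness in the outcome, and neither term is given a criterion.

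Under 'The sensitization and education of social groups', the intervention uses "Health education messages designed to change incorrect beliefs and perceptions, promote correct beliefs and perceptions". The actions taught include "recognizing the symptoms of malaria especially in children under 5 years of age" and taking malaria treatment only after a positive test. 'Objectives' lists the effect on "the knowledge and opinions of respondent female heads of households" about malaria as a secondary objective.

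The end-of-study survey takes place 3 months after the intervention ends ('Population-based household survey'). Interviewers and respondents are not blinded, and some respondents may be social group members ('Randomization').

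The 11% control rate under 'Sample size' comes from a national survey that 'Background' describes as reporting "the percentage of febrile children under 5 years of age who (in the preceding 2 weeks") had blood taken for testing. That denominator is fever alone.

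**The concern.** Fever is a symptom. Suspected malaria, or malaria-like illness, is a view about cause. The trial sets out to change that view in two of its three arms and then uses it, at follow-up, to help decide who is counted. Respondents in educated clusters might stop naming mild untested illness as malaria-like, might stop naming illness that tested negative, or might name more illness because they recognise symptoms better. Each changes the denominator, and the second also changes the numerator, with nobody's testing behaviour altered. The direction cannot be read from the proportions themselves.

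This is separate from misreporting of the test. It touches both co-primary outcomes and the care-seeking and drug-use outcomes built on the same denominators. The analysis described does not remove it:

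- Adjustment uses baseline cluster summaries from different individuals, so it cannot correct a labelling change that arises after randomisation.
- Drawing an equal number of subjects per cluster conceals any difference between arms in the volume of reported illness.

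**Working it through.** **The plan's own figure.** Inputs from 'Sample size': k = 0.16, m = 40 per cluster, 80% power, 5% type I error (two-sided assumed), 11% to 31% and 31% to 51%. With V = p0(1-p0)/m + p1(1-p1)/m + k²(p0²+p1²), clusters per arm are c = 2 + (1.96+0.84)² × V/(p1-p0)².

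- 31% v 51%: V = 0.00535 + 0.00625 + 0.00912 = 0.0207, so c = 6.06 (stated: 6).
- 11% v 31%: c = 4.07.

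The sample size reproduces and is not in question.

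**Effect of changed reporting, true testing held fixed.** The share h is an assumption, shown at 10% and 20%. It is applied to all illnesses of the type named, febrile ones included, so the results are upper-end illustrations.

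- A, share h of untested illnesses no longer reported: p/[1-(1-p)h].
- B, share h of test-negative illnesses no longer reported: with r = 0.49ph, (p-r)/(1-r). The 49% is 100% minus the 51% rapid-test prevalence in the State's under-5s ('Study area'). It is borrowed and is not a positivity rate among ill children who were tested.
- C, extra untested illnesses named, as a share h of the true denominator: p/(1+h).

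| Case | h | 31% reads | 51% reads | 31% arm minus unaffected 11% | 51% arm minus 31% arm, both shifted |
|---|---|---|---|---|---|
| A | 10% | 33.3% | 53.6% | 22.3 | 20.3 |
| A | 20% | 36.0% | 56.5% | 25.0 | 20.6 |
| B | 10% | 29.9% | 49.7% | 18.9 | 19.8 |
| B | 20% | 28.8% | 48.4% | 17.8 | 19.6 |
| C | 10% | 28.2% | 46.4% | 17.2 | 18.2 |
| C | 20% | 25.8% | 42.5% | 14.8 | 16.7 |

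Differences are in points, taken from unrounded values. Each planned difference is 20.

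- Social group v control: +2.3 to +5.0 (A), -1.1 to -2.2 (B), -2.8 to -5.2 (C).
- Social group/provider v social group, shift shared: +0.3 to +0.6 (A), -0.2 to -0.4 (B), -1.8 to -3.3 (C).

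**Power in the dilution case C.** Inverting the same formula at 6 clusters per arm, power is Φ(d√4/√V - 1.96), with d the difference.

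- 11% v 31%: 97% as planned, 93% and 87% at h = 10% and 20% in the intervention arm.
- 31% v 51%, both arms diluted: 79% as planned, then 76% (V = 0.0188, d = 0.182) and 72% (V = 0.0172, d = 0.167).

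**If only the non-febrile limb responds.** Its size is not in the documents. Suppose it is 10% of untested entries and 20% of those drop out. Then h = 0.02 in case A: 0.31/0.9862 = 31.4% and 0.51/0.9902 = 51.5%.

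**Could it create the whole effect?** For 11% to read 31% with testing unchanged, case A needs h = 1 - (0.11/0.31 - 0.11)/0.89 = 72%.

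**The case against.** The strongest reply is that fever alone is enough for entry. A febrile child is counted whatever the respondent thinks the cause was, so opinion directly governs only the non-febrile limb, and the example above shows how small the shift then becomes. This stands, and it is why entry depends only in part on opinion. It does not close the point, because the limb's size is unknown and mild fever is itself recalled and reported by unblinded respondents.

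Exposure is also partial: about four social groups per cluster are educated, and only some respondents will be members. That argues for smaller shares than 10-20%.

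The questionnaire is adapted from a national survey instrument and is not shown, so it may already ask about fever before malaria. That cannot be judged here. The entry and outcome wording that the article does fix still differs in two places and includes the opinion limb.

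A further reply is that the policy target is testing of suspected malaria, so the wider denominator fits the trial's question. This is fair and tells against insisting on fever alone as the primary denominator.

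A reader might infer that up to 6 points of the 20-point difference between 31% and 51% is at risk, from 51% reading as 56.5%. The documents do not support that: the social group/provider arm receives the same social group education, so the shift largely cancels in that comparison, and against control the planned difference for that arm is 40 points. Nor do they support power for 31% against 51% falling from 79% to 59% or 39%. That needs the dilution to occur in the social group/provider arm only; provider communication might add something of its own, but the shared education cannot.

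**Conclusion.** The point holds as a moderate design weakness. Both co-primary denominators are formed at follow-up from unblinded reports that rest in part on an opinion the intervention targets, and the analysis described cannot detect or remove a difference in that opinion between arms.

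The exposed comparison is mainly social group against control, where upper-end assumptions move a 20-point difference by about -5 to +5 points. In the comparison that sets the sample size, a shared shift costs at most about 3 points, and well under 1 point unless extra untested illness is named. These figures rest on assumed 10-20% shares of all illnesses of a type, on an unaffected control arm, and in case B on a borrowed 49% negative share. If only the non-febrile limb responds, they would be smaller.

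A reader might go further and infer that relabelling could produce the planned effect by itself. The arithmetic does not support that, since it would need about 72% of untested illnesses to go unreported. The realistic risk is a distorted estimate or some lost power, in an unknown direction.

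**What to change.** 1. Use one denominator wording in 'Households and community members' and in 'Primary outcome'.
2. At screening, record reported fever in the past 2 weeks for each listed household member before any question mentions malaria, and record malaria-like illness without fever as a separate category.
3. Pre-specify a fever-only analysis of both co-primary outcomes alongside the fever-or-malaria-like analysis. The sponsor may choose which is primary.
4. Report eligible persons per enumerated household member by arm, as a check on differential entry. 'Sampling technique (recruitment)' already plans to enumerate and screen every household.

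The cost is one extra analysis, one tabulation and slightly fewer subjects in the fever-only analysis. If the questionnaire can no longer be changed, item 4 remains possible from the screening records, and item 3 wherever fever was recorded separately. Because fever is also self-reported, these steps reduce the bias and help to bound it but do not remove it.
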